#### Drop-out/retention

Based on our prior studies, we expect a dropout rate of 20% or less through the 32-week study period. Our prior trials with longer protocols had 86% retention after 18 months and 82% retention after 15 months. Retention will be aided by the provision of transportation. Assessments will be attempted with all participants, regardless of study retention. All analyses will follow an intention-to-treat approach that includes all participants randomized to a study group.

##### Aim 1: Effectiveness analysis and hypothesis

Analyses will test our hypothesis that veterans in CBSST-Peer will have superior functioning, recovery, attitude, and skill knowledge outcomes during treatment and follow-up relative to veterans in SST-Peer or TAU, and further that veterans in SST-Peer will have superior outcomes relative to TAU. Secondarily, we will apply all analyses to the symptom measures and explore the impact of gender and racial/ethnicity status where sample size allows. Analyses will follow the same pattern for all the above assessments. We will examine scores obtained at weeks 10 (mid-intervention), 20 (end-of-intervention), and 32 (post-intervention follow-up) as the outcome in HLM, with treatment condition included as a time-invariant covariate, and random intercepts for person and random slopes for time. All available data will be included in accordance with maximum-likelihood estimation procedures with data assumed missing-at-random, an assumption that will be tested with baseline clinical and demographic data. Preliminary analyses will examine potential baseline differences between the three conditions. Relevant covariates including treatment attendance, baseline symptom severity (via BPRS, CAINS), care services, and medications received (standard variables from the PSR toolkit), and demographic variables will be tested and included in the overall model according to model fit. The primary analysis will compare CBSST Peer to SST-Peer and TAU with independent contrasts in the HLM model of all post-baseline time points, to directly test the primary hypothesis that CBSST-Peer has superior outcomes than the other treatments (we will also compare SST-Peer to TAU). As compared to the group by time interaction, this test typically has greater power and is less susceptible to sample-specific artifacts (e.g., regression to the mean, variability in change over time). However, we also wish to examine the degree of change in outcomes over time in CBSST-Peer vs SST-Peer vs TAU. Thus, we will conduct additional analyses to test the treatment condition × time interaction, to examine the question of whether CBSST-Peer has greater improvement in outcomes over time than the other treatments.

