**Self-report measures**	
**Defeatist Performance Attitude Scale (DPAS)**	The DPAS is a 15-item, 5-min self-report subscale of the commonly used 40-item Dysfunctional Attitude Scale (DAS) derived from factor analysis. The DPAS indexes defeatist attitudes about one’s ability to perform tasks [23].
**Independent Living Skills Survey (ILSS) – primary outcome**	The ILSS [24] is a self-report measure of everyday functional living skills for patients with SMI that has proven to be reliable, stable, sensitive, and valid in multiple samples. The 51-item yes-no questionnaire takes less than 10 min to administer and assesses whether or not specific functioning behaviors have been performed over the past month.
**Patient Activation Measure (PAM)**	Patient activation is a self-report measure that refers to the knowledge, skills, confidence, and attitudes patients have for managing health and treatment. The shortened PAM is a 5-min,13-item measure in which respondents endorse items (e.g., “I know what each of my prescribed medications do”) on a scale from 1 (“disagree strongly”) to 4 (“agree strongly”) [25].
**Psychosocial Rehabilitation (PSR) Toolkit**	The PSR Toolkit [22] is a 10-min interview used to collect information on employment, educational activity, and residential situation. In this brief interview, status in each functioning domain is rated on a progressive scale, ranging from the absence of meaningful functioning in the domain to fully independent functioning.
**Recovery Assessment Scale (RAS)**	The RAS [26–28] is a 10-min checklist that assesses aspects of recovery with a special focus on hope and self-determination. The RAS has 41 items on which respondents rate themselves using a 5-point scale ranging from 1 = strongly disagree to 5 = strongly agree. The RAS is intended for use and has been tested with patients with SMI who receive services in outpatient settings and in peer-run programs.

**Table 2 Tab2:** Study outcomes

Domain	Specific measurement	Specific metric	Method of aggregation	Time points
Everyday functioning	Independent Living Skills Survey (ILSS)	Difference in the change from baseline to each follow-up time point, between the three study groups	Mean	Baseline, 10 weeks, 20 weeks, 32 weeks

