### Data collection, data entry, and data management

#### Study interview data

Trained RAs collect data during four assessments at weeks 0 (baseline), 10 (mid-intervention), 20 (end-of-intervention), and 32 (3-month post-intervention follow-up). All data will be maintained in the database using the internal data management tools. The database has been established in such a way that data entry errors (out of bound values) or fields accidentally left blank are immediately flagged. Veterans will be compensated up to $170 (baseline, $25; 10 weeks, $35; 20 weeks, $55; 32 weeks, $55) for completing the study visits.

Data will be kept behind the VA firewall or in locked file cabinets. Identified data will be shared only with regulatory agencies or for patient safety. De-identified data will be shared in compliance with the VA guidelines. Multiple attempts will be made to collect study data from enrolled participants. The study staff will monitor the participants for adverse events in multiple ways. Participants in the two intervention groups will be in close contact with peer specialists, who will report any adverse event they observe. Usual treatment participants will be observed during the four assessment visits and by contact with the participant’s assigned clinical providers.

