### Analyses

#### Statistical analyses

Primary analyses will use hierarchical linear models (HLMs) for continuous variables. The HLMs will include random person-level intercepts and random time slopes. Possible random effects for cohort and peer specialist heterogeneity will be explored. Analyses will include all available data with maximum likelihood estimation, which is preferred over multiple imputations. All tests will be two-sided with alpha = 0.05.

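### The primary ILSS analysis is a contrast of pooled post-baseline scores with no pre-specified baseline ILSS, while Table 2 defines the outcome as change from baseline; the two must be reconciled and baseline adjustment fixed in advance

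*Protocol article*

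**What the plan says.** Protocol article, Aim 1: Effectiveness analysis and hypothesis. The outcome is specified as "We will examine scores obtained at weeks 10 (mid-intervention), 20 (end-of-intervention), and 32 (post-intervention follow-up) as the outcome in HLM". The primary comparison of CBSST-Peer with SST-Peer and TAU is made by "independent contrasts in the HLM model of all post-baseline time points"; the treatment-by-time interaction is an additional analysis.

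Same section, covariates: "Relevant covariates including treatment attendance, baseline symptom severity (via BPRS, CAINS), care services, and medications received", together with demographic variables, "will be tested and included in the overall model according to model fit". Baseline ILSS is not on the list.

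Table 2 (Study outcomes), whose only row is the ILSS, gives the metric as "Difference in the change from baseline to each follow-up time point, between the three study groups".

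Data collection, Study interview data: "Trained RAs collect data during four assessments at weeks 0 (baseline), 10 (mid-intervention), 20 (end-of-intervention), and 32". Table 1 and Table 2 confirm that the ILSS is among the measures taken at baseline.

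Aim 1: Power gives 0.94 at 84 per arm and 0.83 at 67 per arm, for d = 0.35 with 80% retention. The figures come from simulation; neither the simulated model nor the ILSS correlation is given.

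**The concern.** The article defines its primary endpoint twice, and the definitions differ in two respects. The analysis section uses the level of the score, pooled over three visits. Table 2 uses change from week 0, at each visit separately. With three pairs of arms and three follow-up visits, a reader who follows Table 2 could form up to 3 × 3 = 9 differences, where the analysis section has one pooled contrast per pair of arms.

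The plan also leaves a useful covariate without a stated role. The baseline value of the same scale is usually the best single predictor of later scores, and here it is measured before randomisation in every participant. As written it could enter only if a model-fit step selected it, so neither its use nor the resulting precision is fixed in advance. The section defends the post-baseline contrast as more powerful than the interaction test, but does not compare it with a baseline-adjusted contrast. At stake are the precision of the primary comparison and a single, unambiguous primary metric.

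**Working it through.** **Inputs from the article:** 84 per arm (252 in three arms), d = 0.35, "All tests will be two-sided with alpha = 0.05", retention 80% at the last visit, three post-baseline visits.

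**Assumptions:** SD 1 at each visit; a common correlation r between any two ILSS occasions, week 0 included (compound symmetry); an arm effect of 0.35 at every follow-up visit; retention falling evenly to 93%, 87% and 80% at weeks 10, 20 and 32. Since r is not in the article, results are shown over a range.

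**Step 1: the plan's own power.** Power = Φ(d/SE − 1.96). For one visit with all participants, SE = √(2/84) = 0.154, so power = Φ(0.35/0.154 − 1.96) = 0.62; at 67 per arm it is 0.53. The stated 0.94 and 0.83 must therefore rest on repeated measures. For the post-only mean of three visits, 0.94 at 84 per arm needs r of about 0.125 with no dropout, or about 0.05 with dropout to 80%. With baseline adjustment and the same dropout, 0.94 is also reached at r = 0.6. I could not reproduce the stated pair from one set of inputs: at r = 0.6 with adjustment, 67 per arm gives 0.88, not 0.83. The stated power does not reveal which model was simulated.

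**Step 2: variance of the three-visit mean, complete data, relative to one score.**
- Post-only: (1 + 2r)/3
- Baseline ILSS as covariate: (1 + 2r)/3 − r²
- Raw change score: (1 + 2r)/3 + 1 − 2r

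At r = 0.6: post-only 2.2/3 = 0.733; adjusted 0.733 − 0.36 = 0.373; change 0.733 − 0.2 = 0.533. Reduction from adjustment = 0.36/0.733 = 49%.

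| r (assumed) | Post-only | Adjusted | Change score | Variance removed by adjustment |
|---|---|---|---|---|
| 0.3 | 0.533 | 0.443 | 0.933 | 17% |
| 0.4 | 0.600 | 0.440 | 0.800 | 27% |
| 0.5 | 0.667 | 0.417 | 0.667 | 37.5% |
| 0.6 | 0.733 | 0.373 | 0.533 | 49% |
| 0.8 | 0.867 | 0.227 | 0.267 | 74% |

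Adjustment reduces variance at every positive r. The raw change score has more variance than the post-only score when r is below 0.5, so moving the analysis to Table 2's metric as a simple change score is not a safe remedy.

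**Step 3: power with dropout.** Generalised least squares over the dropout patterns, 84 per arm, d = 0.35:

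| r (assumed) | Post-only | Baseline-adjusted |
|---|---|---|
| 0.3 | 0.83 | 0.89 |
| 0.4 | 0.79 | 0.90 |
| 0.5 | 0.75 | 0.91 |
| 0.6 | 0.71 | 0.94 |
| 0.8 | 0.65 | 0.995 |

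Check at r = 0.6: SE falls from 0.1385 to 0.0996. Φ(0.35/0.1385 − 1.96) = 0.71; Φ(0.35/0.0996 − 1.96) = 0.94.

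**The case against.** The strongest reply is that nothing here is invalid. Randomisation makes the post-baseline comparison unbiased, and both metrics have the same expected arm difference at a given visit. The covariate list is open-ended, so baseline ILSS is unnamed rather than excluded, and a condensed article may leave the full covariate set to the SAP. The size of the gain depends on a correlation the article does not give, and compound symmetry is simpler than the planned random-slope model. The comparison also assumes no other covariates, although baseline BPRS and CAINS might recover part of the gain. All of this stands, and it limits the point to precision and consistency. It does not remove the mismatch between the two stated definitions, and selection by model fit is itself a stated rule that leaves baseline ILSS unfixed.

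A reader might infer more than the article supports:

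- **Chance imbalance as a further harm.** At r = 0.6 it contributes r² = 0.36 to the variance factor, which is exactly the 0.733 − 0.373 already counted. It is the same loss.
- **A broken intention-to-treat promise.** The article says "All analyses will follow an intention-to-treat approach that includes all participants randomized to a study group", and a veteran with no follow-up visit adds nothing to a post-only model. The same holds when baseline is a covariate, and in a constrained-baseline model such a record adds almost nothing to the arm contrast. The article also pairs intention to treat with all available data under maximum likelihood.
- **An interaction test blind to early gains.** This would follow if it used only weeks 10, 20 and 32, but the article does not say that it does.
- **Two rival primary results.** The text labels one analysis as primary, and Table 2 prescribes no tests.
- **A wrong power figure.** The simulation may have included baseline; the article does not settle it.

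**Conclusion.** The point holds as one of consistency and efficiency. The analysis section and Table 2 give different primary ILSS metrics, level pooled over visits against change at each visit, and must be reconciled. Leaving baseline ILSS to model-fit selection gives up precision for any positive correlation between visits: about 17% to 74% of the variance for r from 0.3 to 0.8 with complete data. In power, for d = 0.35 at 84 per arm with dropout to 80%, that is 0.83 against 0.89 at r = 0.3 and 0.71 against 0.94 at r = 0.6. These sizes rest on the assumed r, compound symmetry, a constant effect over visits and no other covariates; the direction needs only a positive r. There is no systematic bias.

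**What to change.** - Pre-specify baseline ILSS as a fixed covariate in the primary HLM, exempt from model-fit selection. Alternatively, put week 0 in the outcome with arm means constrained equal there.
- Name one primary metric: the baseline-adjusted mean difference averaged over weeks 10, 20 and 32.
- Edit Table 2 to that metric and list the visit-specific differences as secondary.
- Adjust each secondary scale for its own baseline value.
- State that week 0 is included in the treatment-by-time analysis, if that analysis is to measure improvement from baseline.

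The cost is analysis wording and one table edit, since baseline ILSS is already collected. The change should be made before analysts see outcomes by arm, so that the choice of metric and covariate cannot depend on the results.

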##### Aim 1: Power

Power estimations are from the Stata power simulation package powersim. Data from previous trials and other SST trials were used to obtain effect size estimates to guide simulations of expected ILSS scores in CBSST-Peer, SST-Peer, and TAU. We first estimated power for statistically significant treatment main effect across various sample sizes, assuming 80% retention through the final 3-month follow-up assessment and *α* = 0.05 (two-tailed). For the treatment effects (CBSST-Peer vs. TAU; CBSST-Peer vs. SST-Peer; SST-Peer vs. TAU), we estimate small to medium effect sizes (*d* = 0.35) for ILSS over 20 weeks of treatment and 3-month follow-up. For *d* = 0.35 and retention of 80%, estimated power is 0.94 for *N* = 84 per treatment type and 0.83 for *N* = 67 per treatment type. This is consistent with previous trials of CBSST and SST in which CBSST produced the largest effect sizes (*d* = 0.649) and SST produced improvements, but lower effect sizes [36]. For each group × time interaction effect (comparing each group to each other over time), we project a medium (*d* =0.45) treatment type × time effect size, based on the assumption that CBSST-Peer will produce the largest increase in outcomes per month, based on our prior and other SST trials. For this effect size and our projected enrollment, power for the treatment type x time interaction is sufficient (> 0.80).

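### Covariates for the primary ILSS model are to be chosen by model fit from an open list, so the adjusted primary estimate is not fixed in advance

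*Protocol article*

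**What the plan says.** The Aim 1 effectiveness section of the protocol article names the candidates as "Relevant covariates including treatment attendance, baseline symptom severity (via BPRS, CAINS), care services, and medications received". It adds demographics and states the entry rule: these and the "demographic variables will be tested and included in the overall model according to model fit". It then defines the primary test on the same model: "The primary analysis will compare CBSST Peer to SST-Peer and TAU with independent contrasts in the HLM model of all post-baseline time points". SST-Peer is also compared with TAU.

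The section applies the same approach to all the assessments, so covariate choice is repeated for each outcome. It gives no fit criterion, threshold or order of entry, and no unadjusted or fixed model that would be primary.

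Three other statements bear on the point:

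- Statistical analyses: "All tests will be two-sided with alpha = 0.05", with no allowance for model selection.
- Aim 1, just before the covariate sentence: "Preliminary analyses will examine potential baseline differences between the three conditions".
- Randomization procedures: the data analysts are to be blinded.

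**The concern.** This is a stated rule and not a detail left to an unseen analysis plan. A plan that fixed the covariates would have to contradict the sentence.

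The rule leaves the primary result open in three ways. The list is introduced as non-exhaustive. Fit could mean AIC, BIC, a likelihood-ratio test or a p-value threshold, and these can keep different sets. The search is also repeated by outcome, so ILSS and the other measures may end up adjusted for different things. A p-value or confidence interval from the final model describes a model as if it had been chosen beforehand, and here it will not have been.

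The fault remains even if every candidate is a clean baseline variable. Whether attendance and other post-randomisation variables belong in the model at all is a separate question, and none of the sizes below depends on it.

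**Working it through.** **Inputs from the article.** N = 252 in three arms, taken as 84 each; two-sided alpha 0.05 per test; 80% retention, so 84 × 0.8 = 67.2 per arm; planned effect d = 0.35. The number of covariates, their correlations and their prognostic strength are not given, so they are assumed below.

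**The plan's own figure.** The power section states "estimated power is 0.94 for *N* = 84 per treatment type and 0.83 for *N* = 67 per treatment type". For one score, power = Φ(d/√(2/n) − 1.96):

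- n = 84: Φ(0.35/0.154 − 1.96) = 0.62
- n = 67.2: Φ(0.35/0.173 − 1.96) = 0.53

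For the mean of three scores with variance (1 + 2ρ)/3, n = 84, no dropout and ρ from 0.7 to 0.3, power is 0.72 to 0.87. The stated 0.94 is not reproduced. It came from a simulation whose variance inputs are not shown, so this does not prove an error, and the present point does not rest on it. Only d = 0.35 is used below, as a yardstick.

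**Type I error per contrast, no true effect, nominal 5%.** Both simulations use a linear model on one participant-level outcome.

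| Way of choosing covariates | A: 84 per arm | B: 67 per arm |
|---|---|---|
| Fixed list | 5.0–5.1% | 4.6–5.3% |
| Backward selection by AIC or p < 0.05 | 5.1–5.5% | 4.7–5.5% |
| Favourable model within 2 AIC units | 6.6–7.1% | not run |
| Smallest p over 39 models, ignoring fit | not run | 11–16% |

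- A: 10 or 14 candidates correlated 0.2, three prognostic (coefficients 0.25, 0.20, 0.15), 4,000 to 9,000 trials per setting.
- B: 8 independent covariates, total R² 0.2 or 0.4, 3,000 trials each; simulation SE √(0.05 × 0.95/3000) = 0.004. The 39 models are none, all, the backward-selected one, 8 singles and 28 pairs (3 + 8 + 28).

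**Movement of the estimate.** In A the contrast differed by 0.03 to 0.04 SD across models within 2 AIC units.

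- Against the planned effect: 0.03/0.35 = 9% to 0.04/0.35 = 11%.
- Against the standard error √(2/84) = 0.154 SD: 0.19 to 0.26 of one standard error.

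A hand check gives the same order. Dropping a covariate changes AIC by about t² − 2, so a covariate with |t| = 2 costs 2 units. With unit residual SD its coefficient is about 2/√252 = 0.126. A chance imbalance of one standard error, 0.154 SD, moves the contrast by 0.126 × 0.154 = 0.019 SD. Two such covariates acting the same way move it by 0.039 SD.

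**Effect on the verdict.** With a true effect at about 50% power, significance differed between near-equal models in 8 to 10% of trials. The 50% is an assumption chosen to represent a borderline trial. At the planned 0.94 the share would be smaller.

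**The case against.** The strongest objection is that the rule as written does little harm. Entry is by fit and not by the treatment contrast, and in both simulations mechanical selection cannot be told apart from a fixed list, or nearly so. The 7% figure requires someone to choose on the contrast, which the text does not prescribe and which blinded analysts could not readily do. The shift is about a quarter of a standard error at most. The simulations also use a participant-level linear model, not the planned hierarchical model, with assumed covariates. All of this stands and sets the size of the point.

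It does not dispose of the point. Blinding restrains the direction of a choice but does not say which of several acceptable models is primary. It may also be incomplete, because attendance is a named candidate and TAU participants have no classes to attend.

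A reader might infer from the order of the sentences that covariates enter because arms differ significantly at baseline. The text does not support this. Differences are only to be examined, no significance test is mentioned, and the stated criterion for entry is fit. Calculations of how often some baseline test would be falsely positive are therefore not relevant. In simulation B, choosing covariates by imbalance gave 3.9 to 4.8%, so it was not inflated.

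**Conclusion.** The point holds as a matter of pre-specification. Covariates for the model carrying the primary ILSS contrasts are picked by an undefined fit criterion from an open list, separately for each outcome, so the adjusted primary estimate is not fixed in advance.

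It would be tempting to say that fit-based selection in itself invalidates the 5% level. Neither the document nor the simulations support that: applied mechanically and blind to the contrasts over baseline covariates, the rule leaves error near 5%. The exposure is the latitude the wording leaves: about 7% if the favourable near-equal model is kept, more under a search that ignores fit, and a shift of about 0.03 to 0.04 SD. These sizes rest on assumed covariate numbers, correlations and strengths. The change is worth making because it costs almost nothing and removes an avoidable challenge to the primary result.

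**What to change.** Remove fit-based selection from the primary model. Before outcome data are released, name a fixed list of baseline variables, for example baseline ILSS, baseline BPRS total, the two baseline CAINS factors, age and sex. Baseline ILSS should be on the list because Table 2 defines the outcome as change from baseline, whereas the Aim 1 model uses post-baseline scores and does not name baseline ILSS among its candidates.

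Use the same list for all three contrasts, whatever the fit or observed imbalance. For the other measures, replace baseline ILSS with the baseline value of that measure. Report any fit-selected model only as a sensitivity analysis, with its criterion stated.

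The cost is wording, since the scales are already measured at baseline and demographics are already candidates. Six covariates take participant-level residual degrees of freedom from 252 − 3 = 249 to 243. If some prove not to be prognostic, the loss is negligible.
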